## Abstract

**Background:**

Attention Deficit Hyperactivity Disorder (ADHD) is the most prevalent childhood psychiatric condition with profound public health, personal, and family consequences. ADHD requires comprehensive treatment; however, lack of communication and integration across multiple points of care is a substantial barrier to progress. Given the chronic and pervasive challenges associated with ADHD, innovative approaches are crucial. We developed the digital health intervention (DHI)—CoolTaCo [Cool Technology Assisting Co-regulation] to address these critical barriers. CoolTaCo uses Patient-Centered Digital Healthcare Technologies (PC-DHT) to promote co-regulation (child/parent), capture patient data, support efficient healthcare delivery, enhance patient engagement, and facilitate shared decision-making, thereby improving access to timely and targeted mental health intervention for children at significant risk for poor outcomes. The present paper will describe our planned protocol to evaluate the efficacy of CoolTaCo via randomized control trial (RCT).

**Methods/design:**

We will recruit 60 children (ages 8–12) with ADHD who will be randomized to either immediate (*n* = 30) or delayed (*n* = 30) treatment (i.e., a waitlist control group). Among those randomized to immediate treatment, half will be assigned to DHI (delivered via a smartwatch and smartphone application), the other half to an active control treatment as usual (TAU). Unlike the DHI group, the TAU group will receive the smartwatch with no assigned activities, applications, or interventions on the devices. The intervention period will last 16 weeks; after a participant has been in the delayed treatment group for 16 weeks and has completed the post-waiting period assessment, they will be randomly assigned to either the intervention or active control group. Thus, 30 participants will complete the intervention, and 30 will complete the active control, with half of the total sample completing a waitlist period.

**Discussion:**

Individuals with ADHD have complex needs. Despite improvement in outcomes following cognitive behavioral therapies (CBT) and pharmaceutical treatment, long-term maintenance is a challenge often not addressed by traditional medical approaches, and, as we described, ineffective approaches to information sharing across points of care create further barriers to progress. Our research will fill a significant gap in translating early treatment investments and gains into long-term, sustainable outcomes.

This study was registered as a clinic trial at ClinicalTrials.gov (Digital Health Intervention for Children With ADHD, ID# NCT06456372) on 06/13/2024.

## Background

Attention Deficit Hyperactivity Disorder (ADHD) is the most prevalent and widely recognized psychiatric condition affecting children and adolescents, marked by symptoms of inattention, hyperactivity, and impulsivity [1]. Data from the 2016–2019 US National Survey of Children’s Health (NSCH) (2016–2019) revealed that an estimated 6 million (9.8%) US children aged 3–17 years have been diagnosed with ADHD [2]. ADHD has a significant impact on academic performance, social relationships, emotional well-being, behavior, and family dynamics and can co-occur with conditions such as mood disorders and learning disabilities [3, 4]. Therefore, ADHD treatment necessitates long-term maintenance and self-regulation [5]. ADHD requires comprehensive treatment and typically involves multiple points of care such as primary care clinics (e.g., pediatricians), mental health clinics (e.g., psychiatrists, psychologists, and other therapists), and homes and schools (e.g., special education services) [6]. Consistent and effective communication across points of care is essential to help children effectively manage their ADHD. However, such consistent communication is rare [7]. Despite decades of research on evidence-based medical and behavioral treatments, adherence to treatment is a considerable challenge [8].

Furthermore, long-term maintenance is challenging and presents a second significant barrier to progress that is not met by current approaches [9, 10]. Because ADHD challenges are, for most individuals, persistent and lifelong, substantial self-regulation is needed to support initial treatment gains [11, 12]. Moreover, as children with ADHD become adolescents, they often receive less frequent treatment and support for their difficulties despite facing increasingly challenging situations in academic (high school or college curriculum) [13], social settings (exposure to illicit drugs, alcohol), and interpersonal relationships (e.g., family, romantic, friendship) [14]. Research has shown that adolescents with persistent ADHD are more likely to engage in serious risk behaviors (e.g., underage drinking, reckless driving, and illegal drug use) [15, 16]. Self-regulation is a robust predictor of positive outcomes, and late childhood to early adolescence is a critical period for promoting self-regulation to prevent life-altering mistakes rooted in high school years [17].

Given the chronic and pervasive challenges associated with ADHD, innovative approaches for supporting children and adolescents are crucial [18, 19]. Providing assistance and reinforcement with wearable and mobile technologies offers promising results for children and adolescents [20]. Digital Health Interventions (DHIs) can promote self-regulation (which includes self-monitoring) of health behaviors and facilitate more timely and accurate information sharing between multiple points of care. DHIs could substantially alter the current paradigm, leading to long-term improvements in ADHD outcomes [18, 21]. These technologies, however, have traditionally been designed for individual users and without substantial input from children with ADHD and their families [22, 23]. Our goal is to evaluate an evidence-based and integrated (smartwatch and smartphone) DHI that can increase parent–child support and multidisciplinary communication [24]. *The present paper describes our planned protocol to evaluate the efficacy of the DHI CoolTacCo [Cool Technology Assisting Co-regulation] *via* randomized controlled trial (RCT).*

## Methods/design

### Preliminary work influencing current study protocol

With funding from the Agency for Healthcare Research and Quality, we developed and piloted a DHI called CoolCraig, a wearable and connected system combining a smartwatch and a mobile phone application that provides self-and co-regulation strategies to support caregivers and children with ADHD [8, 18, 21, 25–28]. Our research showed that CoolCraig could support self-regulation in children and co-regulation processes between parent and child. The results also revealed a need for improved instructional guidance and coordination across the multiple points of care [29, 30]. Such results informed our goal of expanding the CoolCraig system and developing the DHI, CoolTaCo [Cool Technology Assisting Co-regulation].

### CoolTaCo

The CoolTaCo System will include a smartwatch app for the child and smartphone app for the parent. As a platform to develop the smartwatch and phone application, we will use the Apple digital ecosystem (i.e., Apple Watch and iPhone). In this manner, we leverage existing Apple Watch features to support intervention, collect and report data (e.g., calendar reminders, activity, sleep, and heart rate data collection and reporting), and a parent iPhone application paired with the child’s Apple Watch. The application will allow parents to enter goals for children (e.g., goals established in therapy or in collaboration with a child’s teacher), approve goals the children initiate for themselves, and create rewards for their child.

Derived from prior ADHD RCTs and implemented in our community programs, CoolTaCo will also include mini-lessons that are created for children and parents on topics such as assertiveness and communication. Key themes of those lessons include ‘Assertion,’ ‘Ignoring Provocation,’ ‘Organization/Executive Function Planning,’ ‘Productivity,’ ‘Self-Regulation,’ and ‘Problem Solving.’ Brief lessons support the key themes with the aim of reducing maladaptive behaviors (aggression, whining/complaining, avoiding non-preferred tasks, disorganization, losing items) and reinforcing the development of an increase in adaptive behaviors necessary for optimizing academic and social outcomes. Figure 1 depicts an example of a mini-lesson which is part of the unit on the social skill of ‘Assertion,’ in which children are prompted to use a self-evaluation strategy when met with a challenge, disappointment, or frustration.

**Fig. 1 Fig1:**
[figure not shown]
Child mini-lesson example on social skills

The CoolTaco System will also deliver parent interventions derived from evidence-based parent ADHD training programs developed and studied in prior ADHD clinical trials and delivered in our community-based parent education programs. Figure 2 depicts an example of a mini-lesson which is part of the main behavioral parent training unit on using communication strategies in efforts to increase the likelihood that a child will follow directions. In this lesson, parents learn that some communication strategies are more effective in specific settings than others and they learn how to identify when and where to choose from a ‘toolbox’ or variety of different ways of using effective communication as an antecedent for increasing desired behaviors.

**Fig. 2 Fig2:**
[figure not shown]
Parent mini-lesson example

The CoolTaco System allow children and caregivers to build self-regulation by setting goals and monitoring and evaluating progress. CoolTaco will also support self-efficacy by helping children and caregivers to reflect on successes and behaviors that need to change. Goals can be set in multiple domains, customized to the treatment plan. In addition to behavioral goals, goals can address hours of sleep per night, amount of physical activity, and medication regimen compliance. Once goals are set, progress can be tracked both daily and weekly. The use of goal-setting, daily self-monitoring, and updating personal goals will promote self-regulation; in addition, it can provide data to be shared with parents and the child’s clinician(s) or educators regarding progress meeting treatment goals. In our clinical practice and research with children with ADHD, common barriers to change include lack of consistency implementing strategies and forgetting to use strategies, both of which are addressed by the system design. CoolTaco will provide an appealing, sustainable intervention that can reinforce positive health behaviors over time.

### RCT design

We will recruit 60 children (ages 8–12) with ADHD who will be randomized to either immediate (*n* = 30) or delayed (*n* = 30) treatment (i.e., a waitlist control group). Among those randomized to immediate treatment, half will be assigned to DHI (an intervention delivered via a smartwatch for the child and smartphone application for the parent), and half will be assigned to an active control [treatment as usual (TAU)] group. Individuals in the TAU group will receive the smartwatch with no assigned activities or applications. The intervention period will last 16 weeks, and participants will complete study assessments before, during, and after the intervention period. Participants randomized to delayed treatment will wait for 16 weeks; they will complete an assessment before and after the waiting period. After this waiting period, they will be randomly assigned to either DHI or TAU. Thus, 30 participants will complete 16 weeks of DHI, and 30 will be followed for 16 weeks of TAU, with half of the total sample also completing a waitlist period.

We will loan smartwatches and phones as necessary for the study in both the DHI and the TAU groups. Participants will be taught basic cybersecurity and privacy best practices, including how to lock and encrypt phone data.

#### Participants

We will recruit children and one of their parents/guardians/caregivers from a local school for children with ADHD and local clinics. If additional parents/guardians/caregivers wish to enroll, their participation will be included as a covariate in our analyses. Participants will also include primary points of care such as educators and clinicians working with the enrolled child participants. 

When a child and parent enroll, we will ask them to indicate the primary points of care for their child. These may include a pediatrician or family doctor, a psychiatrist, a psychologist, a counselor, a teacher, or another individual providing care/intervention for the child. We will ask for consent to approach these individuals to ask for their participation in the research; the burden on these individuals will be minimal. We will aim to gather information about the impact of the DHI on information-sharing, decision-making, and collaboration at multiple points of care. We will aim to recruit at least two individuals representing additional points of care so that for each child, we have at least three points of care (e.g., home, school, mental health therapist) in addition to direct engagement with the patient (child).

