#### Assessments

Participants will have four assessments: Baseline (1 week before the start of the intervention period), Week 8 of the intervention period, Week 16 of the intervention period (post-treatment), and 8 weeks later (follow-up). Delayed treatment (DT) participants will have an additional assessment that follows the waitlist period (Pre- Intervention). This design will create a starting point for future studies of longer-term outcomes that are presently beyond the scope of the proposed study. Completing the study measures will require up to one hour for the child and parent at each assessment. For clinicians and educators, completing the questionnaires will require approximately 20 min at each time point. In addition, at each assessment time point, we will conduct semi-structured interviews (~ 30 min each) with participants focused on issues specific to different points of care and experiences with the DHI. Assessments will take place within a 7-day window at each designated timepoint. We will schedule them at a time convenient to participants and will offer remote/virtual platforms to increase adherence.

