### Quantitative data collection

We will collect quantitative data using (1) well-validated research measures and (2) data gathered from the DHI itself. In this way, we can triangulate the phenomena we observe and create robust models for self-regulation, response to various contextual cues, and our approach's feasibility, acceptance, and potential impact. Standardized outcome measures (see Table 1) will be administered at each assessment timepoint. Quantitative data from outcome measures will be collected to examine both proximal and distal outcomes in a longitudinal repeated measures design. Measures will assess behavioral mechanisms (e.g., self-regulation and self-monitoring), clinical outcomes (e.g., ADHD symptoms), and process outcomes (e.g., patient or provider experience with treatment).

**Table 1 Tab1:** Standardized quantitative outcome measures

Outcome	Data Sources	Instrument	Description
Child Self- Regulation *(primary outcome)*	Child, Parent, Teacher, Researchers	The Behavior Assessment System for Children (BASC-3) – Self, Parent, and Teacher Reports	BASC-3—a validated and nationally normed self-report scale of self-regulation, emotional, and behavioral symptoms that has been shown to produce reliable scores and has national norms for various symptom subscales
Parent Self- Regulation *(primary outcome)*	Parent	BASC-3 Parenting Relationship Questionnaire (PRQ)	The BASC-3 PRQ includes items that address Parent Self-Regulation, Parenting Confidence, and Parenting Stress
Self-Efficacy *(secondary outcome)*	Child	BASC-3 Self-Report	Self-ratings on self-efficacy, a dimension reflecting competence, capability, and problem-solving. The BASC-3 has three scales that address this domain, which will be examined: Sense of Inadequacy, Self-esteem, and Self-Reliance
Parent–Child Relationship *(secondary outcome)*	Child & Parent	BASC-3 Parenting Relationship Questionnaire (PRQ) BASC-3 Self Report (Relations with Parent scale)	The BASC-3 PRQ is a measure of a parent’s perspective on the parent’s relationship with the child. Our primary focus will be on the Relational Frustration scale The BASC-3 Self-Report measure for children includes scores for a subscale that addresses the parent–child relationship (Relations with Parent). Those scores will be examined to assess the impact of DHI on the parent–child relationship

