#### Planned analysis

Multilevel model analyses will be used to adjust for the non-independence (i.e., autocorrelation or clustering) of repeated observations nested within the same individual mixed effects. Such analysis will examine how outcomes within each patient change over time and how individual trajectories of change differ across patients. For each outcome, a mixed-effect model will be estimated with SAS PROC MIXED to test outcome differences between treatment groups at each repeated assessment and differences in the outcome trajectories. Momentary data collected via the scheduled DHI (CoolTaCo) entries will be aggregated to the weekly level, and generalized linear mixed effect models with Poisson distribution for count data will be estimated using SAS PROC GLIMMIX. Tukey adjusted tests will be used for post-hoc comparisons to evaluate significant changes between two time points, treatment groups, or other paired comparisons when a significant interaction was revealed.

Preliminary analyses will be conducted to identify potential individual characteristics (e.g., gender) to be included as covariates. An important strength of multilevel models is the ability to account for unbalanced and/or missing data (which are common problems in ecological momentary data collection) by not placing restrictions on the number of observations obtained for each individual and allows trajectories across time to be estimated from an individual’s available data.

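### Raters are named at enrolment, but delayed children start DHI or TAU 16 weeks later: re-confirm raters at Pre-Intervention, and put cohort in the DHI–TAU model

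*Protocol article*

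**What the plan says.** On raters, the Participants section says: "When a child and parent enroll, we will ask them to indicate the primary points of care for their child". Consent to approach those people follows, and Potential problems and strategies repeats the arrangement. Neither section says whether the raters are confirmed or replaced later. Under Assessments, clinicians and educators fill in questionnaires at every time point.

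Their ratings belong to primary outcomes. For child self-regulation, Table 1 lists "The Behavior Assessment System for Children (BASC-3) – Self, Parent, and Teacher Reports". For shared decision-making it lists a provider/educator version of the Working Alliance Inventory.

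On timing, RCT design says: "Participants randomized to delayed treatment will wait for 16 weeks; they will complete an assessment before and after the waiting period". Only then are these children randomised to DHI or TAU, and "The intervention period will last 16 weeks". The Assessments section adds a visit for this half: "Delayed treatment (DT) participants will have an additional assessment that follows the waitlist period (Pre- Intervention").

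On analysis, RCT design counts 30 DHI and 30 TAU across both halves, while Study sample size lists four groups of 15 separated by immediate or delayed start. Planned analysis says: "For each outcome, a mixed-effect model will be estimated with SAS PROC MIXED to test outcome differences between treatment groups". It does not say whether that means two groups or four, and it leaves covariates to preliminary analyses.

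**The concern.** Naming raters at enrolment suits the immediate half, whose intervention begins about a week after the first assessment. For the delayed half, the same rule picks raters 16 weeks before allocation and roughly 33 weeks before the main post-treatment rating. Teachers in particular may have stopped working with the child by then. The result would be a missing rating, or a change score in which a change of rater is mixed with the child's own change. Teacher reports are worth protecting because they come from outside the family, which knows its allocation.

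A second, smaller matter comes from the same two-cohort structure. DHI or TAU is assigned within the immediate and the delayed cohort, and the cohorts differ in waiting time, prior testing and calendar period. A factor within which allocation is made belongs in the model by design. It should not depend on what a preliminary screen of covariates turns up.

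**Working it through.** **The plan's own figure.** The only computed figure is 81% power for 60 children. It cannot be reproduced, because the article gives no numerical effect size, no correlation between repeats and no test family. This point does not rest on it.

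**Timeline.** Inputs from RCT design and Assessments: first assessment 1 week before the start, wait 16 weeks, intervention 16 weeks, follow-up 8 weeks after Week 16.

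| | First assessment to Week 16 | First assessment to follow-up |
|---|---|---|
| Immediate | 1 + 16 = 17 weeks | 1 + 16 + 8 = 25 weeks |
| Delayed, from the pre-wait assessment | 1 + 16 + 16 = 33 weeks | 1 + 16 + 16 + 8 = 41 weeks |
| Delayed, from Pre-Intervention | 16–17 weeks | 24–25 weeks |

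Without the pre-start week, 41 becomes 40. Counted from Pre-Intervention, the delayed half has about the same span as the immediate half.

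**Illustration of exposure (assumed calendar).** The article gives no school-year length or enrolment dates. Assume a school year of 36–40 weeks and enrolment spread evenly over 52 weeks. The share of children whose assessments all fall in one school year is max(0, school-year weeks − span)/52:

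- 17 weeks: 19/52 to 23/52 = 37–44%
- 33 weeks: 3/52 to 7/52 = 6–13%
- 25 weeks: 11/52 to 15/52 = 21–29%
- 41 weeks: 0%

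The complements matter as much. In the immediate half, 56–63% would fail the test by Week 16 and 71–79% by follow-up. If children start only during the school year, a 25-week schedule runs past its end in 25/40 to 25/36 = 63–69% of cases, and a 41-week schedule always does. These figures describe the calendar; they are not rates of rater change.

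**Cost of a changed rater (assumed correlations).** Baseline-adjusted residual variance is proportional to 1 − r². If a change of rater lowers the pre–post correlation from 0.7 to 0.5, the ratio is 0.75/0.51 = 1.47. If it lowers it to 0.4, the ratio is 0.84/0.51 = 1.65. So residual variance rises by 47–65%, in the affected children only.

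**Cost of leaving cohort out (assumed inputs).** Take 30 v 30, a standardised difference of 0.73, cohorts balanced within arm, and a two-sided 5% t test. An omitted cohort shift of g SD multiplies the residual variance by 1 + g²/4, so the effective difference is 0.73/√(1 + g²/4).

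| Cohort shift g | Variance factor | Power without term | Power with term |
|---|---|---|---|
| 0 | 1.00 | 79.4% | 79.4% |
| 0.2 | 1.01 | 79.0% | 79.4% |
| 0.5 | 1.0625 | 77.0% | 79.4% |
| 0.8 | 1.16 | 73.3% | 79.4% |

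With no cohort difference, the degree of freedom spent on the term (58 to 57) costs nothing visible.

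**The case against.** The strongest reply is that an omission is being read as a rule. The article says when families are asked, not that the raters are then locked, and it describes educators and clinicians as people working with the enrolled child. Replacing raters is operational detail that a condensed article may leave to the full protocol. This is fair, and it rules out saying that the plan forbids an update. What remains is that the one time point the article gives for choosing raters is poorly matched to half the sample.

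A second reply is that the long spans matter only if the pre-wait visit is the baseline for DHI against TAU. The sample size rests on four repeated measures, while delayed children have five assessments. The natural four are therefore Pre-Intervention, Week 8, Week 16 and follow-up. That is the likely intention, but the article does not say so, and one sentence would settle it.

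A reader might also infer that delayed children's outcomes do cross school years and do change rater. The article does not support this. It gives no calendar, a clinician need not change with the school year, and a teacher at a specialised school may stay. Nor is the risk confined to the delayed half.

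Nor does the article support an inference of bias. Each cohort is split between DHI and TAU, so season, waiting and rater turnover should fall on both arms alike.

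Finally, it is not established that the model ignores cohort. Four groups are listed in one place, treatment groups are undefined in another, and model terms may stand in an analysis plan that is not shown. This makes the cohort limb the weaker of the two.

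**Conclusion.** The point holds as a low-cost improvement to precision and completeness. The timing mismatch follows from the stated schedule: 16 weeks between naming raters and starting DHI or TAU, about 33 weeks to Week 16 and about 41 to follow-up in the delayed half. The likely harm is noise and missing ratings in the teacher BASC-3, and less so in the provider/educator Working Alliance Inventory. Its frequency cannot be computed from the article; the shares above rest on an assumed school year and an assumed enrolment pattern. The gain from a cohort term is modest, from nothing to about 6 percentage points of power (79.4% against 73.3%) over assumed cohort shifts of 0 to 0.8 SD.

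**What to change.** Make these changes:

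- For delayed children, re-confirm or re-nominate the teacher and provider raters at the existing Pre-Intervention assessment, before the second randomisation, so that the choice of rater cannot depend on allocation.
- Record the rater's identity at every assessment in both cohorts.
- State that, for delayed children, the four time points of the DHI–TAU contrast are Pre-Intervention, Week 8, Week 16 and follow-up.
- Include cohort (immediate or delayed) as a fixed term in the DHI–TAU models, whatever the preliminary covariate analyses show.

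The cost is protocol wording, a nomination step at a visit that already takes place, some repeat consent of educators, and one model degree of freedom.
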